##### Anthropometrics

The child’s height (cm) and weight (kg) are objectively measured using standard operating procedures with a mounted stadiometer and portable scale. BMI (weight/height^2^) will be calculated and compared with national growth standards to calculate BMI *z* score and categorize weight status [46].

##### Cognitive and Motor Skills

These constructs are measured using the recent update of the National Institutes of Health Toolbox V3 [47]. Preschoolers complete the cognitive tasks validated for this age range and consolidated from the previous version (V2) [48,49]. The tests and associated constructs are picture vocabulary test (language), visual reasoning (nonverbal and visual reasoning), picture sequence memory test (episodic memory), and speed matching (processing speed) [50]. The preschooler also completes the National Institutes of Health Toolbox Early Childhood Motor Battery, which includes the tests and constructs as follows: 9-hole pegboard dexterity test (fine motor), grip strength (muscular strength), standing balance (balance), and 2-minute walk endurance test (muscular endurance). The preschooler completed the cognitive measures on a tablet, while the motor skills were completed with a trained administrator.

##### Behavioral Problems and Executive Function

Preschoolers’ executive function and behavioral problems are assessed during this study. Parents complete questions with Likert scale responses from the Behavioral Assessment System for Children (3rd edition) related to child behavioral problems, and the Behavioral Rating Inventory of Executive Function Preschool for executive function [51], which will then be used to calculate the preschool child’s T-score for analysis. Both questionnaires are valid tools and have shown to be useful tools for assessing child development [51,52].

##### Descriptive Characteristics

Home, parent, and child-level correlates, along with parent habit and M-PAC components, are collected**.** Home space and equipment are assessed by a parent report inventory of preschooler-appropriate availability and accessibility of PA (eg, jump rope) and media (eg, television) equipment, room design, and sleep components. This updated inventory is based on validated inventories in parents of older children [53] and preschoolers [54,55]. Household organization was assessed using the Confusion, Hubbub, and Order Scale, which is a 15-item measure assessing disturbance, organization, and noise levels in the home. It has been validated in parents of young children [56].

Parent-level correlates include parent support for PA, parent screen time practices, and bedtime and family routines. Parents complete a 4-item questionnaire to assess parental support of child PA based on a validated questionnaire in this age range [57], which includes core support elements, including encouragement, logistics, and coparticipation [58]. Parents report their perceived influence on their child’s screen media use and limit setting of screen media from a validated questionnaire for parents of preschool children (12 questions total). These scales had high internal consistency (0.84-0.86) and correlation with child BMI and screen time [59]. Parents are asked 7 questions on family regularity, including having a bedtime ritual and regularity of family meals over the last week, based on a validated questionnaire for preschoolers [60].

Child-level correlates include solely child preferences. Parents complete questions, including “*when outside, my child prefers*” with a list of activity options, “*my child’s physical activity is limited due to their interest or motivation*,” and their child’s preference for PA in their free time, with Likert scale options for each question. These scales had high internal consistency (0.60) and correlation with child screen time [59].

Finally, parental support for PA and sleep and limiting screen time is examined using self-report items of habit formation to establish routines for each behavior [61], and an adapted questionnaire measuring intention and behavioral support for all 3 movement behaviors based on the reflective, regulatory, and reflexive parts of the M-PAC model [11].

### Stipends and Incentives

Intervention participants can redeem points achieved through engagement with the mobile app for up to US $75 worth of incentives. Examples of incentives are activities to do at home to encourage PA (eg, child wearable device) and sleep (eg, sound machine), and reduce screen time (eg, puzzles) [11].

### Analytical Approach

#### Randomization and Blinding

Participants are randomized to intervention or control in a 1:1 ratio with block randomization stratified by age and sex, with a random allocation process developed by a biostatistician. Due to the nature of the study, staff administering the first visit are unblinded to group assignment.

##### Aim 1: Meeting 24-Hour Movement Guidelines

We will compare the proportion of intervention and control group participants meeting all 3 recommendations at 12 weeks using a chi-square analysis.

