### Measures

#### Primary Outcome

Our primary outcome is adherence to all 3 of the 24-hour Movement Guidelines. Preschoolers’ PA and sleep were assessed in 15-second epochs using the Actigraph GT3X+ accelerometer. Preschoolers wear this device on their wrist using a Velcro band, only removing it for water-based activities (eg, bath). Accelerometer data will be evaluated using the Sadeh algorithm to detect sleep periods and compared with the parent-report of sleep [33]. Periods of ≥20 minutes of continuous zeroes during the day will be removed as nonwear time [34,35]. Validated cut points for wrist measurement in this age range will be used for sedentary behavior (0-328 counts per 5 seconds), light PA (329-1392 counts per 5 seconds), and MVPA (≥1393 counts per 5 seconds) [36]. Total PA is the sum of light PA and MVPA. Preschoolers with ≥3 days (at least 1 weekday and 1 weekend day) of ≥10 hours of wear, and 3 days of sleep, will be included for analysis, similar to another wrist-worn protocol [37], and is the estimated minimum for accelerometer wear in this age range [38,39]. To capture adherence to the sedentary screen time guideline, parents are asked, “On an average 24-hour period, how much time does your child spend using electronic screen devices (such as a smartphone, tablet, video game, or watch television or movies, videos on the internet) while they are sitting or lying down?” with a free response option. This question is conducted at screening and subsequent visits and was chosen to align with surveillance efforts of movement behaviors [40]. This questionnaire reflects the previous week before accelerometer wear. The sum of guidelines obtained based on these measures, and if the participant meets all 3 guidelines, will be used for analysis.

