#### Sample Size and Power Calculation

Our analysis is based on a previous home-based routine-based multibehavior intervention in preschool children, which sought to improve similar behaviors, and reported an increase in the proportion of children meeting the screen time guideline increased from 5% to 30% over 12 weeks [23]. Based on our past studies, we estimate that few will meet the screen time guideline [25,62], like the beginning metric of the routine-based study. Given the overlap in content between the routine-based study and this study, we hypothesize that we can also improve the screen time guideline and potentially the remaining behaviors within the same time frame. A minimally important difference in 24-hour movement behaviors is not clear as of October 2025, as there are no other 24-hour movement guideline adherence studies. A sample size of 30 families per arm will provide 80% power to detect a meaningful difference in the proportion of control (1/30, 5%, no change from baseline) and intervention group (10/30, 35%) participants meeting all 3 recommendations at the 12-week visit. Assuming a dropout rate of 25%, we will recruit 40 families per arm (80 total). This power and difference can also be achieved with a minimum of 24 participants per group; while 30 participants per group will have 63.5% power to detect a difference between 5% and 25%, meeting all 3 recommendations; and a 99% power to detect a difference between 5% and 20%, meeting all 3 recommendations. Statistical significance will be set at *P*=.05 for all aim-related analyses.

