#### Exploratory Aims

We will also conduct an intent-to-treat analysis using a log-binomial regression or Poisson with robust variance to adjust for baseline recommendation number and randomization strata (age and sex). Linear regression will also be used to compare changes in exploratory outcomes between treatment and control groups with adjustment for baseline values. If demographic differences, such as income, are found between the 2 groups, we will conduct a sensitivity analysis with these variables for adjustment. These exploratory outcomes include, in priority order: number of recommendations obtained (range: 0-3), individual 24-hour movement behaviors, anthropometry, early child motor battery scores, early child cognitive battery scores, executive functioning scores, and behavioral problem scores. Descriptive characteristics will also be explored, such as PA and accessibility score, household chaos score, parental support of PA, parental perceived influence on screen time, family regularity index, child preferences for PA, and theoretical component changes (eg, intention and behavioral support for PA). We will also explore the ideal change in behaviors using isotemporal substitution analysis, whereby evaluating substitution of one behavior (eg, sedentary behavior) for another (eg, MVPA) with change in child developmental outcomes.

Furthermore, we will examine the relationship between meeting specific recommendations and child outcomes, with a mediator of theoretical component changes (eg, habit formation scores). Mediation analysis will be conducted using the PROCESS vs 3.5 macro with 10,000 bootstrap intervals with unstandardized estimates and CIs [63]. These exploratory outcome testing will be subject to the Benjamini-Hochberg adjustment for multiple comparisons [64].

As for missing data, we will describe differences in baseline characteristics between participants with complete versus incomplete follow-up. Sensitivity analyses based on multiple imputation methods will be conducted to examine the robustness of our findings with respect to missing data.

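### The only strata-adjusted model of guideline adherence (log-binomial or robust Poisson) has no finite risk ratio when an arm has no events, and at the plan's 5% rate it can print spurious significance

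*Protocol article*

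**What the plan says.** The protocol article defines the outcome under Primary Outcome: "Our primary outcome is adherence to all 3 of the 24-hour Movement Guidelines". Under Randomization and Blinding, families are "randomized to intervention or control in a 1:1 ratio with block randomization stratified by age and sex". Under Aim 1, the confirmatory comparison is of the proportions "meeting all 3 recommendations at 12 weeks using a chi-square analysis", with no stratum term.

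The strata appear in one model only. Under Exploratory Aims, an intent-to-treat analysis is to use "log-binomial regression or Poisson with robust variance to adjust for baseline recommendation number and randomization strata (age and sex"). That sentence does not repeat the outcome. A log-binomial model needs a binary one, and meeting all three guidelines is the natural reading. For the other exploratory outcomes, "Linear regression will also be used to compare changes in exploratory outcomes between treatment and control groups with adjustment for baseline values", again without strata.

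The expected event counts come from Sample Size and Power Calculation: "control (1/30, 5%, no change from baseline") against "intervention group (10/30, 35%) participants meeting all 3 recommendations at the 12-week visit".

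**The concern.** A risk ratio divides by the control risk. With a planned control rate of 5% and about 30 evaluable children, an arm with no events is an ordinary outcome. The log-link model then has no maximum-likelihood estimate: the coefficient drifts until the software stops. Robust Poisson, the named alternative to log-binomial, does not escape this. Its sandwich standard error stays small while the coefficient runs away, so the printed P value is extreme whatever the data say.

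This model is the only analysis labelled intent-to-treat, the only one that uses the strata, and the only adjusted analysis of the primary outcome. It would naturally be reported beside the chi-square. A non-significant primary result could then stand next to an adjusted P value near zero that rests on one child.

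**Working it through.** **Inputs.** From Sample Size and Power Calculation: control 5% (the printed fraction, 1/30, is 3.3%), intervention 35%, 30 evaluable and 40 recruited per arm, significance level 0.05 (two-sided assumed).

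**The plan's own figures.** 30/(1 − 0.25) = 40 per arm, as stated. Exact power at 30 per arm for 5% vs 35% is 78.8% with Fisher or the Yates-corrected chi-square, close to the stated 80%, and 88.0% with the uncorrected chi-square.

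**Chance that the control arm is empty, (1 − p)^n.**

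| Evaluable controls | p = 5% | p = 1/30 |
|---|---|---|
| 30 | 0.95^30 = 21.5% | 36.2% |
| 38 | 14.2% | – |
| 40 | 12.9% | 25.8% |

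**Chance that exactly one arm is empty if both are truly 5%, 2q(1 − q) with q = 0.95^n.**
- n = 30: 2 × 0.2146 × 0.7854 = 33.7%.
- n = 38: 2 × 0.1424 × 0.8576 = 24.4%.

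**What robust Poisson prints with an empty control arm** (unadjusted, HC0 variance; the software reports convergence).

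| Control vs intervention | Robust Poisson P | Uncorrected chi-square P |
|---|---|---|
| 0/30 vs 1/30 | 1.7 × 10^-95 | 0.31 |
| 0/30 vs 2/30 | about 10^-195 | 0.15 |
| 0/30 vs 3/30 | printed as 0 | 0.076 |

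In the first row the coefficient is 20.4 and the standard error 0.98, so z = 20.4/0.98 = 20.8. The coefficient is only where the iterations stopped. The standard error is the intervention arm's contribution alone, √[(29/30)/(30 × 1/30)] = √0.967 = 0.98. The empty arm has residuals near zero and adds nothing visible.

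Adjusting for strata and baseline count does not help. With 0/30 vs 10/30, Poisson and log-binomial both give a log risk ratio of about 22. The robust standard error is about 0.27 (P about 0), while the model-based one is about 13,000 to 14,000 (P about 0.999).

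**False-positive rate.** In 3,000 simulated trials with both arms at 5%, 30 per arm, and adjustment for assumed binary age and sex (baseline guideline number left out), robust Poisson rejected in 34.9% and the chi-square in 2.5%. All the robust Poisson rejections came from trials with exactly one empty arm, which fits the 33.7% above. At 38 per arm the rate is 24%. The exact size of the chi-square at 30 per arm is 2.8%.

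**Does leaving the strata out of the chi-square matter?** Simulated at 30 per arm, with assumed stratum rates, against a Cochran-Mantel-Haenszel (CMH) test:
- Size at 5% in both arms: 2.6% to 2.8% for each test.
- Power, 5% vs 35%, flat strata: CMH 87.9%, chi-square 88.0%.
- Power, 5% vs 35%, prognostic strata: CMH 88.4%, chi-square 87.2%.
- Power, 5% vs 25%, flat strata: CMH 62.3%, chi-square 63.1%.

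A visible size gap (chi-square 3.7%, CMH 5.3%) appears only with a 20% null rate and strongly prognostic strata. Under similarly strong strata, power at 5% vs 25% is 65.2% for CMH and 62.9% for the chi-square.

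**The case against.** The model is exploratory, and no confirmatory conclusion depends on it. That stands: with an empty control arm the chi-square is still computable (0/30 vs 10/30 gives P = 0.0005).

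At the planned effect the damage is limited. If the control arm is empty and the intervention rate is 35%, four or more intervention events make the chi-square significant, and that happens 99.8% of the time. The two analyses then agree in direction, although no usable risk ratio can be reported. The false positives belong to the case of little or no effect.

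A coefficient above 20, or a model-based standard error in the thousands, would alert a careful analyst. That is fair, but the plan names the robust variance, which hides the second sign, and the software reports convergence. The Benjamini-Hochberg adjustment cannot correct P values of this size.

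The 21% assumes that only 30 controls are evaluable. The Results section reports one loss among 39 randomized, and with 38 to 40 controls the figure is 13% to 14%. Against that, the accelerometer wear rule can remove further children. A control rate below 5% would raise the figure, and it is plausible because eligible children meet at most one guideline by parent report.

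A zero-event fallback is detail that an article may leave to an analysis plan. That is true, and its absence is not the point here. The point is that the models actually named misbehave at the event rate the article itself plans for.

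A reader might also infer that the primary chi-square is wrong because it ignores the randomization strata, or that it wastes material power. The documents do not support this. Nothing in them says that sex, or age within 3 to 4 years, predicts adherence, and at the planned rates the two tests are almost identical. A simple primary test with an adjusted supporting model is a common design.

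**Conclusion.** The concern holds for the exploratory adjusted model. At 5% in controls that model has no finite risk ratio in 21% of trials with 30 evaluable controls (13% with 40). If both arms are truly at 5%, its robust Poisson form rejects in about 35% of trials at 30 per arm (24% at 38), against about 3% for the chi-square. These figures rest on a true rate of 5%, a two-sided 5% level, binary age and sex, and a model without the baseline guideline number.

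The primary analysis is not in error. The unadjusted chi-square is valid and at most slightly conservative. Stratifying it changes power by about −1 to +1 percentage point at the planned rates, so that part is optional.

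**What to change.** Before the data are analysed, replace the log-binomial or robust Poisson model under Exploratory Aims with an estimator that tolerates zero cells. One choice is Firth-penalized logistic regression adjusted for age, sex and baseline guideline number, reporting standardized risks in each arm and their difference with a confidence interval. The cost is some shrinkage of the estimates and a model fitted on the odds scale. It needs no new data and uses standard software.

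Optionally, make the primary test a CMH test stratified by age and sex, with a stratified risk difference and 95% confidence interval. This matches the analysis to the randomization at negligible cost, but it should not be presented as a correction or as a gain in power.

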##### Aim 2: Feasibility

We will average the Likert scale responses (ranges 1.0-5.0) across all weeks completed (up to 12). Feasibility and acceptability will be achieved if the average response is ≥4.0/5.0 for each category.

#### Sample Size and Power Calculation

Our analysis is based on a previous home-based routine-based multibehavior intervention in preschool children, which sought to improve similar behaviors, and reported an increase in the proportion of children meeting the screen time guideline increased from 5% to 30% over 12 weeks [23]. Based on our past studies, we estimate that few will meet the screen time guideline [25,62], like the beginning metric of the routine-based study. Given the overlap in content between the routine-based study and this study, we hypothesize that we can also improve the screen time guideline and potentially the remaining behaviors within the same time frame. A minimally important difference in 24-hour movement behaviors is not clear as of October 2025, as there are no other 24-hour movement guideline adherence studies. A sample size of 30 families per arm will provide 80% power to detect a meaningful difference in the proportion of control (1/30, 5%, no change from baseline) and intervention group (10/30, 35%) participants meeting all 3 recommendations at the 12-week visit. Assuming a dropout rate of 25%, we will recruit 40 families per arm (80 total). This power and difference can also be achieved with a minimum of 24 participants per group; while 30 participants per group will have 63.5% power to detect a difference between 5% and 25%, meeting all 3 recommendations; and a 99% power to detect a difference between 5% and 20%, meeting all 3 recommendations. Statistical significance will be set at *P*=.05 for all aim-related analyses.

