A mobile health (mHealth) modality (eg, mobile apps) can address behavioral patterns by delivering context-based information to parents. Parent-based mobile apps have been effective in reducing preschooler sugar-sweetened beverage consumption [19] but have yet to be translated to improving 24-hour movement behaviors. This paucity is demonstrated in a recent systematic review of digital health interventions for preschool PA, where the authors found 8 interventions in total, and only 1 was a parent-based mobile health app [20]. This mobile health app demonstrated effectiveness on child health behaviors, including PA, suggesting these modalities can be used to reach parents and impact child health behaviors [21]. Together, these modalities provide an opportunity to build upon previous work and change movement behaviors, especially for those at risk for poor adherence to the 24-hour Movement Guidelines.

The overarching aim is to conduct a study to evaluate the effectiveness and feasibility of a 12-week mHealth home-based intervention on 24-hour movement behaviors in preschoolers who meet few guidelines (zero or 1 guideline). Primary outcomes include device-based and self-report measures of 24-hour movement behaviors, and the secondary outcome is the feasibility and acceptability of the app. Exploratory outcomes include preschoolers’ cognitive and motor skills, changes within the home environment, and behavioral control processes. We hypothesize that children will increase the number of recommendations obtained, with 35% of preschoolers meeting 24-hour Movement Guidelines (all 3 recommendations), based on other routine-focused interventions [22,23]. We also hypothesize parents will report the intervention is feasible (≥4.0/5.0 on Likert scale).

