### Participants, Eligibility, and Recruitment

To be included, parents must report that their preschooler meets zero or 1 guideline for PA, sleep, and screen time as defined by the World Health Organization at the screening call [1]. Zero or 1 guideline was chosen as existing prospective studies demonstrate meeting 1 or zero guidelines is associated with lower motor skills and cognitive development compared with meeting all 3 guidelines [5,24]. Based on work conducted before the COVID-19 pandemic, we anticipated 15%-20% of preschoolers would qualify [5], with similar proportions found in a preschooler-focused systematic review [4]. Adherence to the 24-hour Movement Guidelines by parent report was chosen to reduce the burden, align with a survey study that informed analysis [25], and ensure the inclusion of the target population. The PA guideline is defined as ≥180 min/d of total PA, including ≥60 min/d of MVPA. The sleep guideline is defined as 10-13 h/d. The sedentary behavior guideline is defined ≤1 h/d of sedentary screen time.

Parents must also agree to use their mobile phone for the study duration (approximately 12 weeks), download the mobile app onto their phone, be fluent in English, and be willing to travel to the research site to complete study visits. Exclusion criteria are mobility limitations as reported by the parent, meeting 2 or 3 of the 24-hour movement guidelines, sibling or household member participating in the study, and parents reporting the preschooler will not wear a device on their wrist.

This study seeks 80 families, with 40 families per arm. Parents of preschoolers (aged 3-4 y) are recruited from a metropolitan area of a Midwest US state. We plan to recruit through the institution’s research-based list-serves (including local children’s hospitals), a local advertisement through social media, blogs, magazines, community-based efforts (eg, childcare centers and local events), and at local medical centers. Recruitment efforts include flyers and paid advertisements.

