### Comparison With Previous Work

To the authors’ knowledge, there is only one other 24-hour movement-focused intervention, as the current 24-hour movement scientific landscape is predominantly observational studies [9]. That study was also a 12-week randomized controlled trial with wait list control in 147 young children, and it demonstrated significant decreases in screen time but no intervention effect in other behaviors [9,67]. Major differences between the past trial and this trial include (1) population (this trial: 3-4 y who meet 0 or 1 guideline, past trial: 3-5 y who meet 0-2 guidelines), (2) intervention approaches (multibehavior and transfer theory vs all 3 behaviors at once and integrated), (3) outcomes (adherence to 24-hour Movement Guidelines vs Activity Sleep Index), and (4) intervention methods (all mobile app vs internet-based education and online workshops) [9]. It is unclear if this study’s different populations, intervention approaches, modalities, and outcomes will result in significant results, but there will still be a noticeable contrast.

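### The quoted source supports a screen-time rate of 30%, not the 35% assumed for meeting all three guidelines; power at lower rates is well under 80% unless the control rate is near zero

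*Protocol article*

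**What the plan says.** The primary outcome is adherence to all three 24-hour guidelines (Primary Outcome), compared between arms at 12 weeks by chi-square (Aim 1).

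Under Sample Size and Power Calculation, the calculation is based on an earlier home-based intervention that reported "an increase in the proportion of children meeting the screen time guideline increased from 5% to 30% over 12 weeks". The all-three comparison is then set as "control (1/30, 5%, no change from baseline") against "intervention group (10/30, 35%) participants meeting all 3 recommendations at the 12-week visit". The conclusion is "A sample size of 30 families per arm will provide 80% power to detect a meaningful difference", and then "Assuming a dropout rate of 25%, we will recruit 40 families per arm (80 total"). The step from screen time to the other behaviours is worded as a hypothesis, with no figure. The section also says that the minimally important difference is not clear.

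The Introduction repeats the target, "with 35% of preschoolers meeting 24-hour Movement Guidelines (all 3 recommendations), based on other routine-focused interventions", citing references 22 and 23. Reference 23 is the screen-time study above. No figure from reference 22 is reported.

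The section adds lower-effect scenarios at 30 per arm: 63.5% power for 5% versus 25%, and 99% for 5% versus 20%. It also says that 24 per group would give the same 80% for 5% versus 35%.

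**The concern.** The source result concerns one guideline and the endpoint requires three. Meeting all three is a subset of meeting screen time, so in any one sample the all-three rate cannot be higher than the screen-time rate. The plan assumes more on the composite (35%) than its quoted source reached on a single component (30%).

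The control rate has the same origin problem. The 5% equals the source's screen-time baseline, yet it is described as no change from baseline on all three guidelines. For entry, "parents must report that their preschooler meets zero or 1 guideline", so by parent report nobody enters meeting all three.

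What is at stake is the credibility of the power statement. A reader is told that the trial has 80% power, and the 99% scenario suggests that this survives a much smaller effect. It does not at the stated 5% control rate.

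**Working it through.** **Inputs.** 30 analysable families per arm, 1:1 allocation, control 5%, intervention 35%, significance level 0.05, chi-square test: all from the article. Two-sided testing is my assumption, because the article does not state it.

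**Step 1: the plan's own figures.**

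Dropout: 30 / (1 − 0.25) = 40 per arm. Reproduced.

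Exact power is the sum, over all pairs (x, y), of Bin(x; 30, pC) × Bin(y; 30, pI), counting only pairs where the test gives P ≤ 0.05. For 5% versus 35%:
- Fisher's exact test: 78.8%
- uncorrected chi-square: 88.0%

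Pooled normal approximation, with mean rate 0.20:

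z = [0.30 − 1.96 × √(2 × 0.20 × 0.80 / 30)] / √(0.05 × 0.95 / 30 + 0.35 × 0.65 / 30) = (0.30 − 0.2024) / 0.0957 = 1.02, so power is 84.6%.

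The 80% is therefore sound for 35%, and closest to Fisher. The other printed figures fit uncorrected methods instead. At 24 per group, uncorrected chi-square gives 80.8% and Fisher 70.6%. For 5% versus 25% at 30 per group, chi-square gives 63.3% and Fisher 43.6%, against 63.5% printed. The section thus appears to mix methods without naming them. The printed fractions also do not match their percentages: 1/30 = 3.3% and 10/30 = 33.3%.

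**Step 2: the bound.** P(all three) ≤ P(screen time). If screen time here reaches the source's 30% and no more, the all-three rate is at most 30%. It equals 30% only if every child who meets screen time also meets physical activity and sleep. The article gives no figure for that overlap, so the rates below 30% are scenarios.

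**Step 3: power at lower rates, 30 per arm (uncorrected chi-square / Fisher).**

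| Intervention rate | Control 5% | Control 0% |
|---|---|---|
| 35% | 88% / 79% | >99% / 98% |
| 30% | 78% / 63% | 99% / 92% |
| 25% | 63% / 44% | 96% / 80% |
| 20% | 45% / 24% | 88% / 57% |
| 15% | 26% / 9% | 68% / 29% |

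The 0% column can be checked by hand. With no control responders, chi-square first rejects at 4 of 30: 60 × (4 × 30)² / (30 × 30 × 4 × 56) = 4.29, above 3.84 (3 of 30 gives 3.16). Fisher first rejects at 6 of 30: P = 2 × C(30,6)/C(60,6) = 0.024 (5 of 30 gives 0.052). Power is then P(Y ≥ 4) or P(Y ≥ 6) for Y ~ Bin(30, pI). At 21% this gives 90% and 62%.

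**Step 4: the 99% scenario.** With the same n and the same control rate, a smaller difference cannot have more power than a larger one, so 99% for 5% versus 20% cannot stand beside 63.5% for 5% versus 25%. By the pooled formula, z = [0.15 − 1.96 × √(2 × 0.125 × 0.875 / 30)] / √(0.05 × 0.95 / 30 + 0.20 × 0.80 / 30) = (0.15 − 0.1674) / 0.0832 = −0.21, so power is 42%. The exact values are 45% and 24%.

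**The case against.** The strongest reply is that 30% is not a fixed ceiling. The logical limit is the screen-time rate in this trial, which may exceed the earlier study's, and the article presents the extension to other behaviours as a hypothesis. This stands, so the bound must be stated conditionally.

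Reference 22 is also cited for the 35% and its content is not available here. This stands too. A reader might infer that the attribution to earlier interventions is false and should be deleted. The documents do not support that; they only fail to show which figure supports 35%.

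At exactly 30% the shortfall by uncorrected chi-square is small (78% against 80%). Retention may also beat the assumed 75%: the Results section reports one loss among 39 randomized by October 2025. With all 40 per arm analysed, chi-square power is 89% at 30% (Fisher 82%). At 20% it is still only 57% (41%).

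The two doubts pull in opposite directions, since a control rate near 0% raises power. That is correct, but 0% by parent report does not fix the rate on the outcome measure. Physical activity and sleep are then measured by accelerometer, and the article's limitations acknowledge possible misclassification between the two.

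A reader might also take the one other 24-hour movement trial, where "it demonstrated significant decreases in screen time but no intervention effect in other behaviors", as evidence that the composite will not move. The article lists differences from it in population, approach, outcome and delivery, so it is weak evidence either way.

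Finally, the article discloses 63.5% at 25%, so it does not claim 80% throughout. The 99% printed next to it undoes that disclosure.

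**Conclusion.** The point holds as a gap between the effect assumed and the source quoted for it. A reader might infer that the 80% is miscalculated; it is not, for 5% versus 35%. What lacks support is the 35%, and to a lesser degree the 5%, as rates for all three guidelines.

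With control at 5% and 30 analysed per arm, power is 78% (Fisher 63%) at the source's own rate and falls to 26% (9%) at 15%. This rests on two-sided 0.05 and on screen time doing no better here than in the source. The rates below 30% are illustrative, because the overlap with physical activity and sleep is not given. A control rate near 0% would recover much of the loss, by an amount that depends heavily on the test.

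A reader might go further and say that a null result would be misread as failure of the app. The article does not say so, and rules for reading a null result commonly belong in the analysis plan.

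**What to change.** Keep 80 families. In Sample Size and Power Calculation:

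1. State that the 5% to 30% figure is for the screen-time guideline alone, and that 35% on all three is an assumption; or report the figure from reference 22 that supports it. Align the Introduction.
2. State the basis of the 5% control rate on the outcome measure.
3. Name the test and sidedness behind the power figures, and use one method throughout.
4. Replace the lower-effect scenarios, including the 99%, with a recomputed power table over intervention rates of 15% to 35% and control rates of 0% to 5%. Make the fractions and percentages agree.

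The cost is text and a short recalculation, with no extra families. The downside is that the stated power looks less favourable.
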